### Primary outcome and analysis timepoint

The primary outcome for this study is change in OKS from baseline to 12 months. A 12-month period has been selected as the prespecified time point for the main analysis, as it represents a clinically meaningful period in which to assess functional change and weight management interventions, while also minimising loss to follow-up.

### Long-term outcomes

Participants will be consented to long-term data linkage with the National Joint Registry (NJR) and Hospital Episode Statistics (HES).^33 34^ This will allow data linkage for subsequent surgical interventions, hospital admissions and other relevant healthcare utilisation beyond the 24-month follow-up period. The 24-month PROMs and registry linkages will therefore be analysed and reported as secondary/long-term outcomes and reported separately from the main 12-month study outcomes.

### Protocol registration and deviations

The protocol was prospectively registered on ISRCTN (ISRCTN42984928, https://doi.org/10.1186/ISRCTN42984928). The design, eligibility criteria, outcomes and planned analyses described in this manuscript are consistent with the registered protocol.

No substantive deviations from the preregistered protocol have occurred. Any future protocol deviations arising during study conduct will be reported transparently in subsequent results publications in accordance with standard reporting practice.

### Sample size calculation

Previous studies at our centre predicting PROMs in knee pathology reported R² values, the proportion of the variance in outcomes accounted for by the explanatory data (ie, regression model terms), of approximately 30%. Using a more conservative R² of 20% (effect size=0.25), a sample size of 76 was estimated as required to achieve 90% power at a 5% significance level for a cross-sectional primary analysis at 12 months. For the longitudinal analysis (baseline, 6 months and 12 months), applying a design effect of 1.1 (assuming Intraclass Correlation Coefficient=0.05) increased the required sample to 84. Accounting for an expected 20% loss to follow-up, we aim to recruit a minimum of 105 participants with BMI ≥35 kg/m^2^ for the primary analysis.

In addition to the main cohort (BMI ≥35 kg/m^2^), baseline data will be collected from a comparator group with BMI <35 kg/m^2^. The original funding application assumed a BMI distribution of ~52% with BMI ≥35 kg/m^2^ and ~48% with BMI <35 kg/m^2^. However, early recruitment data indicate the actual clinical distribution is approximately 66% BMI <35 kg/m^2^ and 33% BMI ≥35 kg/m^2^. Based on this assumed split, we plan to recruit all eligible patients consecutively, regardless of BMI category, until a total sample of 400 is achieved. Given the expected split between those under and over the BMI threshold of 35 kg/m^2^, this should ensure we recruit approximately the required number of participants (n=105) for the primary analysis in the high BMI group. This sample size is consistent with the published guidelines for the planned exploratory modelling and hypothesis generation.^35 36^

This approach ensures that our final cohort will reflect the population presenting to secondary care, rather than enforcing an artificial quota by BMI category. While the comparator group of participants with BMI <35 kg/m^2^ will not be included in the primary analyses specified in this protocol, these data will be used for exploratory modelling and hypothesis generation. The study is therefore adequately powered for the planned analyses while remaining representative of the underlying clinical population.

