**Methods and analysis:**

This study will recruit 400 participants with severe Kellgren-Lawrence grade four knee osteoarthritis from eight secondary care centres in England. All participants, irrespective of BMI, will provide baseline clinical data and patient-reported outcome measures (PROMs), enabling characterisation of baseline associations between BMI, knee function and body image.

A prespecified subgroup of participants with BMI ≥35 kg/m^2^ (minimum n=105) will undergo longitudinal follow-up at 6 months, 12 months and 24 months, including repeat BMI measurement, PROMs and detailed data on access to surgical and non-surgical interventions, including weight-loss strategies and TKR. For those with BMI ≥35 kg/m^2^, statistical modelling will be used to explore associations between baseline factors and longitudinal outcomes including Oxford Knee Score and weight change at 12 months (n≥105). Structural equation modelling will be used to quantify associations between BMI and knee pain/function mediated by psychosocial factors using data from all participants (n=400). A nested qualitative study of surgeons and patients will explore obstacles and preferences in the management of severe knee osteoarthritis.

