### Study aim

To examine management pathways and longitudinal outcomes in people with BMI ≥35 kg/m^2^ and severe knee OA referred to secondary care and to characterise baseline patient-reported outcomes across BMI categories.

Objectives:

Explore and model to what degree the interactions between baseline factors described in the prior objective, treatments received after recruitment and weight change predict knee function at 12 months after presentation to secondary care in this population.Qualitatively explore patient and surgeon experiences of treatments for high BMI and knee pain.Describe and quantify the relationship between underlying constructs measured by key patient-reported outcome measures for both obesity and knee-related pain and function at baseline across BMI categories.

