
### Follow-up assessments

The follow-up questionnaire will collect data on participants’ weight, weight-loss treatments that participants have received and treatments for their knee and their outcomes.

At 6 months, 12 months and 24 months, the same PROMs collected at baseline (OKS, APQ, Body-Q, EQ-5D) will be readministered, with the addition of the Global Rating of Change Scale.^32^ This is a seven-point scale ranging from ‘no change or condition has worsened’ to ‘a great deal better’. This will provide a reference point against which changes in other PROMs can be interpreted, helping to distinguish meaningful improvement from measurement variability.

Participants will additionally be asked the following questions about previous knee treatments at each follow-up assessment: have they had a knee replacement or other knee surgery, physiotherapy and/or a steroid injection in the last 6 months and/or are they on a waiting list for knee replacement surgery.

Participants will also be asked about weight loss treatments including whether they have had weight loss surgery, taken prescribed medications for weight loss, attended an NHS-referred structured weight loss programme or dietary modification programme and/or they meet the minimum NHS-recommended exercise recommendations.

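### The 76/84/105 sample size implies an overall R² test of about six terms; the model described is larger, and power for single predictors is not addressed

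*Protocol article*

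**What the plan says.** All references are to the protocol article.

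- **Sample size calculation.** The effect size is set as "Using a more conservative R² of 20% (effect size=0.25"), and "a sample size of 76 was estimated as required to achieve 90% power at a 5% significance level". Next, "applying a design effect of 1.1 (assuming Intraclass Correlation Coefficient=0.05) increased the required sample to 84". Finally, "Accounting for an expected 20% loss to follow-up, we aim to recruit a minimum of 105 participants" with BMI ≥35 kg/m². The section ends: "The study is therefore adequately powered for the planned analyses". It gives no number of predictors. It also expects about 33% of 400 recruits to have BMI ≥35 kg/m².
- **Statistical analysis.** A longitudinal linear regression is to identify the variables that predict OKS at 12 months. The explanatory variables include EQ-5D, BMI change, adherence to treatments, TKR and BODY-Q.
- **Baseline data collection.** Two BODY-Q subscales are used.
- **Follow-up assessments.** Knee treatments are asked about item by item. So are weight-loss treatments: "whether they have had weight loss surgery, taken prescribed medications for weight loss, attended an NHS-referred structured weight loss programme" or a dietary programme, and exercise.
- **Study aim, objectives.** The model is to examine how far interactions between baseline factors, "treatments received after recruitment and weight change predict knee function at 12 months".
- **Abstract, Methods and analysis.** The 12-month models, including "weight change at 12 months (n≥105"), carry the figure of 105.

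**The concern.** A power calculation for R² in multiple regression needs three inputs: the effect size, the sample size and the number of terms. The third is missing, so a reader cannot tell which model the 90% refers to. If 76 was derived for a small model and a larger one is fitted, the overall test has less power than stated.

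There is also a mismatch of question. The calculation concerns whether the model as a whole explains any variance. The analysis is meant to say which variables predict OKS, and that rests on individual coefficients. A general statement of adequate power invites readers to treat a non-significant coefficient as evidence that the variable does not matter. The Discussion expects these results to help shape national guidelines, so that reading would have consequences.

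**Working it through.** **Inputs from the article.** R² = 0.20, alpha = 0.05, power 90%, base N = 76, design effect 1.1, 84 after the design effect, 20% loss, minimum recruitment 105, expected share 33% of 400.

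**Method.** Overall F test of R² = 0 with k terms: numerator df = k, denominator df = N − k − 1, noncentrality λ = f²·N, where f² = 0.20/0.80 = 0.25.

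**Step 1: reproduce the plan's figure.** At N = 76, λ = 0.25 × 76 = 19.

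| k | Power at N = 76 | N for 90% |
|---|---|---|
| 5 | 92.0% | 72 |
| 6 | 89.9% | 76.2 (77 rounded up) |
| 7 | 87.7% | 81 |
| 8 | 85.5% | 85 |
| 12 | 76.6% | 99 |

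Only k = 6 fits. Its unrounded chain also matches: 76.2 × 1.1 = 83.9, and 83.9/0.8 = 104.8, against the stated 84 and 105. The design effect is 1 + (3 − 1) × 0.05 = 1.1. Under the alternative convention λ = f²·(N − k − 1), 90% needs 72 for four terms and 78 for five, so 76 would imply a still smaller model.

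**Step 2: count the terms described.**
- Adherence as one term: EQ-5D 1 + BMI change 1 + adherence 1 + TKR 1 + BODY-Q 2 = 6. This leaves no room for any baseline factor or interaction, both of which the objective names.
- Treatments entered separately: EQ-5D 1 + BMI change 1 + TKR 1 + BODY-Q 2 + other knee surgery, physiotherapy and steroid injection 3 + weight-loss surgery, medication, structured or dietary programme, and exercise 4 = 12, again before baseline factors and interactions.

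The article does not fix the coding of adherence, so 12 is an inferred count.

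**Step 3: power with 12 terms.** On the plan's own terms, 84 evaluable counts as 84/1.1 ≈ 76. The expected yield is 0.33 × 400 = 132 recruited, 132 × 0.8 = 105.6 evaluable, and 105.6/1.1 = 96 effective.

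| Evaluable | Design effect kept | Design effect ignored |
|---|---|---|
| 84 (planned minimum) | 76.6% (N = 76) | 82.5% (N = 84) |
| about 105 (expected) | 89.0% (N = 96) | 92.4% (N = 105) |

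For 90% with 12 terms, N = 99 is needed, which is 99 × 1.1 = 109 after the design effect and 109/0.8 = 137 recruited (both rounded up). An effective 96 gives 90% for 11 terms.

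**Step 4: single coefficients.** As an illustration only, share R² = 0.20 equally over the terms. With six terms each has f² = (0.20/6)/0.80 = 0.0417, and power for one coefficient at N = 76 is 42%. With 12 terms each has f² = (0.20/12)/0.80 = 0.0208, and power is 24% at N = 76 and 26% at N = 84. Conversely, 90% power for one coefficient needs a partial R² of about 12.5% at N = 76 and 11.4% at N = 84, almost independently of k.

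**The case against.** **The arithmetic is sound.** The chain 76, 84, 105 reproduces for six terms, and the named variables make exactly six if adherence is a single term. This stands: there is no miscalculation. But the objective's baseline factors and interactions then have no place in the powered model.

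**Coding of covariates belongs in the analysis plan.** This stands for the coding, so 12 cannot be presented as the article's own number. It does not cover the article's statement of power, which depends on a number of terms that it does not give.

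**105 is a minimum, and more are expected.** This stands. At about 105 evaluable, 12 terms give about 89% with the design effect kept. A reader might infer that the study is underpowered or that the adequacy statement is plainly false. The documents do not support that for the overall test at the expected yield.

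**R² = 20% is conservative.** The centre's earlier studies gave about 30%. At that value f² = 0.30/0.70 = 0.43, and 12 terms give about 96% at N = 76 and 98% at N = 84. This is a fair margin for the overall test, but the stated 90% is tied to 20%.

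**The aim is exploratory, and the equal split is invented.** The 42% is indeed an illustration, and no rule in the article says that non-significant variables will be declared non-predictive. The detectable partial R² needs no such split, and it leads to the same conclusion.

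**The abstract's 105.** A reader might call this an error. It is the recruitment minimum, the model uses all available data, and the expected evaluable number is also about 105. It is a matter of clarity only.

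**Conclusion.** The concern holds in this form: the power statement is wrong as written, because it claims adequacy for the planned analyses on a calculation that covers only an overall R² test with about six terms. The described model has more than six terms on any reading that honours the stated objective.

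The size depends on the number of terms. If it is 12, power at the planned minimum is about 77%, or 82–83% without the design effect. At the expected yield it is about 89%, or 92–93% without it. Terms beyond 12 would lower these figures. All of them assume R² = 20% and noncentrality f²·N, and take the 1.1 design effect at face value.

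The gap for single predictors does not depend on the term count. At the planned minimum, only a variable that explains about 11–13% of the otherwise unexplained variance would be detected with 90% power.

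**What to change.** - State the number of terms behind 76.
- Restate power with the design effect retained, for example: *84 evaluable participants give about 90% power for the overall test with at most six terms; about 105 evaluable give about 89% for 12 terms.* The article reports recruitment as complete, so the actual number with BMI ≥35 kg/m² can replace the expected one.
- Cap the primary model's degrees of freedom to match: six terms at 84 evaluable, or 11 to 12 at about 105. Count baseline factors, interactions and any time terms within the cap.
- Limit the closing adequacy sentence to the overall R² test.
- Add the detectable partial R² for one coefficient, about 11–13% for 90% power at the planned minimum.
- In the abstract, make clear that 105 is the recruitment minimum and 84 the planned evaluable minimum.

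The cost is a text change with a less favourable stated figure. No more patients are needed.

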## Methods and analysis

### Setting and participants

Participants will be recruited from eight secondary referral centres in England:

University Hospitals Coventry & Warwickshire.The Princess Alexandra Hospital NHS Trust.Luton and Dunstable University Hospital.Milton Keynes University Hospital.University Hospitals Birmingham.South Tees Hospitals NHS Trust.Wrightington, Wigan and Leigh NHS Foundation Trust.Northumbria Healthcare NHS Trust.

Recruitment commenced on 17 December 2024 and completed on 19 December 2025.

Inclusion criteria

Referral from primary care to secondary or intermediate care services for knee OA.Severe arthritis as assessed by the treating clinician. Defined as Kellgren-Lawrence grade four primary knee arthritis (severe) in any knee compartment on a knee radiograph (X-ray), or clinician deems arthritis severe enough to warrant a TKR.Aged over 18 years

Exclusion criteria

Presence of inflammatory arthritis.History of intra-articular fracture causing post-traumatic arthritis.Previous surgery on the ipsilateral knee if implants were inserted.Unable or unwilling to comply with follow-up procedures.Unable to provide informed consent (eg, does not have capacity to consent).Insufficient English language skills to understand study materials and respond to questionnaires.

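### The 90% power at the minimum of 105 holds only for a joint test of about six model terms, a number the article does not state and its own model exceeds

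*Protocol article*

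**What the plan says.** All the sample size figures are in the protocol article, Sample size calculation. R² is introduced as "the proportion of the variance in outcomes accounted for by the explanatory data (ie, regression model terms"). The derivation then reads "Using a more conservative R² of 20% (effect size=0.25), a sample size of 76 was estimated as required"; the target is 90% power with alpha 5%, and the analysis is cross-sectional at the 12-month visit. A design effect of 1.1 (intraclass correlation 0.05) raises 76 to 84, and 20% loss to follow-up raises 84 to 105, which the section and the Abstract both call a minimum. The number of model terms is not given.

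On recruitment, the section reports that "early recruitment data indicate the actual clinical distribution is approximately 66% BMI" below 35 kg/m², with 33% at or above it. It plans 400 participants in total and says "this should ensure we recruit approximately the required number of participants (n=105) for the primary analysis in the high BMI group". It concludes: "The study is therefore adequately powered for the planned analyses".

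The model is described in three other places:
- **Statistical analysis** lists five explanatory items: EQ-5D, BMI change, adherence to treatments, receipt of TKR and BODY-Q. The list is introduced as what the variables will include.
- **Baseline data collection** says that two BODY-Q subscales are used.
- **Study aim** has as an objective to model how interactions between baseline factors, treatments received and weight change predict knee function at 12 months. None of the five listed items is identified as a baseline factor.

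Follow-up assessments shows what adherence covers. For the knee, participants are asked "have they had a knee replacement or other knee surgery, physiotherapy and/or a steroid injection in the last 6 months". For weight, they are asked about surgery, medication, a structured or dietary programme, and exercise.

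**The concern.** The power of an overall R² test depends on the number of terms tested as well as on R², alpha and N. Without that number, a reader cannot tell which model has 90% power. If the figure comes from a smaller model than the one described, the adequacy statement covers a different analysis from the one that will be run. At a fixed R² each extra term lowers the power, so the published 90% would be too favourable at the stated minimum. The risk is that an overall null or weak result is read as coming from a 90%-powered analysis when the true figure was lower.

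**Working it through.** **Inputs (Sample size calculation).** R² = 0.20, so f² = 0.20/0.80 = 0.25, as stated. Alpha is 0.05 and target power 0.90. The design effect is 1 + (3 − 1) × 0.05 = 1.1 for three time points. Loss is 20%, the total is 400 and the share with BMI ≥35 is 33%. The number of terms p is not stated and has to be solved for.

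**Method.** Overall F test with p and N − p − 1 degrees of freedom and noncentrality λ = f² × N. At N = 76, λ = 0.25 × 76 = 19.

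**Step 1: reproduce the plan's figure.** N needed for 90% power:
- p = 5: 72
- p = 6: 77 (N = 76 gives 89.9%)
- p = 7: 81

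So 76 corresponds to about six terms. A test of a single coefficient with partial f² 0.25 needs only 45 and does not reproduce it. Then 76 × 1.1 = 83.6, rounded up to 84, and 84/0.8 = 105. The chain is internally correct.

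**Step 2: count the terms described.**
- The five listed items taken literally: 5 terms.
- BODY-Q as its two subscales, adherence still one variable: 6 terms.
- Any baseline factor, interaction or visit term: 7 or more.
- The seven non-TKR treatments as separate terms (other knee surgery, physiotherapy, steroid injection; weight-loss surgery, medication, structured or dietary programme, exercise): EQ-5D 1 + BMI change 1 + TKR 1 + BODY-Q 2 + treatments 7 = 12, before any baseline factor.

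**Step 3: power at the minimum and at the expected size.** The minimum of 105 gives 105 × 0.8 = 84 analysed, and 84/1.1 ≈ 76 effective. The split gives 0.33 × 400 = 132 recruits, and 132 × 0.8/1.1 = 96 effective. The last column takes the N needed for 90% power, multiplies by 1.1, divides by 0.8 and rounds up at each step.

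| Terms | Power at 105 recruited (76 effective) | Power at 132 recruited (96 effective) | Recruits needed for 90% |
|---|---|---|---|
| 5 | 92.0% | 97.3% | 100 |
| 6 | 89.9% | 96.4% | 107 |
| 7 | 87.7% | 95.3% | 113 |
| 9 | 83.3% | 93.0% | 123 |
| 10 | 81.0% | 91.7% | 128 |
| 12 | 76.6% | 89.0% | 137 |

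For 12 terms the last column runs 99 × 1.1 = 108.9 → 109, and 109/0.8 = 136.25 → 137. The six-term row shows 107 rather than 105 because 76 falls just short of 90%.

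**Step 4: the recruitment sentence.** With 400 recruits and a 33% share, the binomial probability of at least 105 high-BMI participants is 0.9985. The expected 132 exceeds the minimum by 27.

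**Step 5: sensitivity to R².** With 12 terms at N = 76, power is 89.6% at R² 25% (f² = 1/3) and 96.5% at R² 30% (f² = 0.30/0.70).

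**The case against.** The strongest reply is that nothing in the section is miscalculated. The chain reproduces at six terms, and the listed variables can be coded as five or six. How adherence is coded is commonly left to an analysis plan or full protocol not shown here. R² of 20% was chosen as conservative against about 30% in earlier work, and a larger model might explain more variance: with 12 terms, R² of about 25% restores 90% at the minimum. The section also presents the sample as suited to exploratory modelling.

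Much of this stands. Two stronger readings should be set aside:
- **That the model needs at least 12 terms.** A reader might infer this from the list of treatments. The wording about compliance with each treatment option belongs to the descriptive summaries and does not specify the regression. Twelve is one plausible coding.
- **That the expected number is wrong because 33% of 400 is 132 and not 105.** The article presents 105 as a required minimum and nowhere forecasts it. An expected 132 meets it almost certainly. The word approximately in that sentence is loose and understates the margin, but it is not an arithmetic error.

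The reply does not remove the main point. The coding of adherence can wait, but the power figure and the conclusion drawn from it are already in print. They fit six terms only if no baseline factor, interaction or visit term enters, whereas the objective calls for baseline factors. If the word interactions there means general interplay rather than product terms, the baseline factors still add to the count. A hoped-for higher R² is not the planning value the section adopted.

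**Conclusion.** The point holds as a conditional power statement whose condition is missing, not as an arithmetic error. The 90% at 76/84/105 is correct for a joint R² test of about six terms, and the article describes a larger model. At the minimum of 105, power is about 88% with 7 terms and 77% with 12. At the 132 that the article's own split predicts, it is 96% with 6 terms and 89% with 12. The shortfall therefore belongs to the stated minimum and not to the expected recruitment, and 132 is the figure that supports adequacy for a larger model.

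This rests on four assumptions: R² stays at 20% whatever the number of terms; the test is the overall F test with λ = f² × N; the 1.1 design effect and 20% loss apply as stated; and the 33% share holds across all 400 recruits. The article does not give the number of terms to be fitted, so the result is a range.

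**What to change.** Change the wording of the Sample size calculation in four ways:
1. State the number of model terms behind 76.
2. Restate joint-test power for the terms to be fitted, at the minimum of 105 and at the expected BMI ≥35 count of about 132. The achieved count can replace the latter, since Setting and participants says "Recruitment commenced on 17 December 2024 and completed on 19 December 2025". Alternatively, fix a six-term model and say so.
3. Apply the 1.1 design effect at both sizes. The 84 analysed correspond to 76 effective, so the 12-term figure at the minimum is 77%; the 82% obtained by entering 84 directly omits the design effect.
4. Limit the adequacy statement to the joint R² test.

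No extra patients or data are needed. The cost is a less favourable power figure at the minimum size, partly offset by the more favourable figure at the expected size.
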